### Patients’ evaluation immediately after treatment

The patients rate the intensity of stiffness at the area of strongest stiffness immediately after the treatment by a VRS (none, weak, moderate, strong, very strong) and on a 100 mm VAS ranging from 0 (no neck/shoulder stiffness) to 100 (most severe neck/shoulder stiffness imaginable). Also the patients rate the change in stiffness in the area of strongest stiffness compare with before the treatment by a VRS (clearly worsen, slightly worsen, no changed, slightly improved, clearly improved). When they rate “clearly or slightly worsen”, they rate the change on a 100 mm VAS ranging from −100 (worsened to the most severe stiffness imaginable) to 0 (no change). When they rate “clearly or slightly improved”, they rated the change on a 100 mm VAS ranging from 0 (no change) to 100 (completely cured no stiffness). For the no-treatment control group, after the 10 min of no-treatment period the patients report the same items.

Excluding no-treatment control group, the patients report what they feel during the treatment. If they feel pain from the treatment, they rate pain intensity on a 100 mm VAS ranging from 0 (no pain) to 100 (most severe pain imaginable). If they feel de-qi from the treatment, they rate de-qi intensity on a 100 mm VAS ranging from 0 (no de-qi) to 100 (strongest de-qi imaginable). Further they rate their pleasantness or unpleasantness to the treatment on a 200 mm VAS ranging from −100 (very unpleasant) to 0 (neither pleasant nor unpleasant) to 100 (very pleasant), and rate their satisfaction with the treatment on a 200 mm VAS ranging from −100 (completely unsatisfied) to 0 (neither satisfied nor unsatisfied) to 100 (completely satisfied).

Then, the patients guess whether the treatment is “penetrating”, “skin-touch” or “no-touch” or to record “cannot identify the treatment” and they report their confidence level in their guesses by a VRS (with confidence, with slight confidence, with little confidence, with no confidence) and on a 100 mm VAS ranging from 0 (no confidence) to 100 (full assurance) [24,28,29].

### Patients’ evaluation 24 hours after treatment

The patients rate the intensity of stiffness at the area of strongest stiffness 24 hours after the treatment by a VRS (none, weak, moderate, strong, very strong) and on a 100 mm VAS. When the patients rate at none, they write when it disappears. Also the patients rate the change in stiffness in the area of strongest stiffness compared with before the treatment by a VRS (clearly worsen, slightly worsen, no changed: returned to the pretreatment condition, slightly improved, clearly improved). When their stiffness return to the pretreatment condition, they record when it returns. When they rate “clearly or slightly worsen”, they rate the change on a 100 mm VAS ranging from −100 (the most severe stiffness imaginable) to 0 (no change). When they rate “clearly or slightly improved”, they rate the change on a VAS ranging from 0 (no change) to 100 (no stiffness: completely cured). For no-treatment control group, the patients report the same items.

Excluding no-treatment control group, the patient guess which type of treatments they receive, and they report their confidence in their guess by a VRS (with confidence, with slight confidence, with little confidence, with no confidence) and on a 100 mm VAS ranging from 0 (no confidence) to 100 (full assurance) [24,28,29].

### Practitioners’ guess as to treatment

After completion of treatment with four needles, the acupuncturists guess whether the treatment is “penetrating”, “skin-touch” or “no-touch” or to record “cannot identify the treatment”; they report their confidence in their guesses by a VRS (with confidence, with slight confidence, with little confidence, with no confidence) and on a 100 mm VAS ranging from 0 (no confidence) to 100 (full assurance) [24,27-29]. Additionally, the acupuncturists indicate which clues influence their guesses, such as the patient’s expression, behaviour, external bleeding, internal bleeding, lack of bleeding, reaction to needle insertion, reaction to needle removal and other clues [24,27].

### Outcomes

#### Primary measurements

Improvement of neck/shoulder stiffness score immediately and 24 hours after the treatment are primary outcomes.

#### Secondary outcome measurements

Practitioners’ and patients’ guesses at treatments and their confidence in their guesses and, pain and de-qi felt during treatment by the patients are secondary outcomes.

### Adverse events

The assistant and the acupuncturists monitor the patients for the presence of adverse events, such as pneumothorax, bleeding, haematoma, dizziness, fatigue and needle pain. The assistant also ask the patients to report if they experience any adverse events during and after acupuncture treatment.

### Statistical analysis

Multiple regression analysis will be applied for data analysis. We will use pre- and post-treatment score changes as primary outcome, and treatment modes (penetrating treatment, skin-touch placebo treatment, no-touch placebo treatment and no-treatment control). Additional covariates will include age, gender and other related potential confounders.

In addition, we will define 30% improvement of stiffness intensity on neck/shoulder after treatment as good responders, the chi-square test will be used to determine whether the numbers of improved patients are different in the penetrating, skin-touch placebo and no-touch placebo treatment groups. All statistical analyses will be performed using SPSS (Statistical Package for the Social Sciences, SPSS Inc. Chicago, IL). The 400 bags will be opened by the researchers to reveal and record the nature of the treatments after all 400 treatments have been completed. The assistants who supported the acupuncture treatments will not take part in this work.

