**Methods:**

Six acupuncturists and 400 patients with functional neck/shoulder stiffness are randomly assigned to four treatment groups: genuine acupuncture penetrating the skin, skin-touch placebo or no-touch placebo needles in a double-blind manner (practitioner-patient blinding) or no-treatment control group. Each acupuncturist applies a needle to each of four acupoints (Bladder10, Small Intestine14, Gallbladder21 and Bladder42) in the neck/shoulder to 50 patients. Before, immediately after and 24 hours after the treatment, patients are asked about the intensity of their neck/shoulder stiffness. After the treatment, practitioners and patients are asked to guess whether the treatment is “penetrating”, “skin-touch” or “no-touch” or to record “cannot identify the treatment”.

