**Figure 1 F1:**
[figure not shown]
Trial flow diagram.

Before the trial, we prepared 100 sets of four genuine acupuncture needles for penetrating treatment, 100 sets of four skin-touch placebo needles for skin-touch placebo treatment and 100 sets of four no-touch placebo needles for no-touch placebo treatment. The 400 bags for sterilisation numbered from 1 to 400 were randomly assigned to the penetrating, skin-touch placebo, no-touch placebo, or no-treatment control arm using a table of random numbers that was generated by the RAND function (Microsoft Excel 2003). Four penetrating needles, four skin-touch placebo needles or four no-touch placebo needles were put in a numbered bag corresponding to the assigned treatment type and sealed by the study controller; then they were sterilised with ethylene oxide gas.

The first to the last patient in order are each assigned one of the 400 numbered bags. As a result, 400 patients are randomly assigned to penetrating, skin-touch placebo, no-touch placebo treatment or no-treatment control. Each of the six acupuncturists treats 50 patients consecutively and in order.

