### Patients’ evaluation of neck/shoulder stiffness before treatment

Before patients’ evaluation, the assistant makes sure the patients fully understand and that they evaluate the amount of neck/shoulder stiffness only on the right or left side whichever the patients feel is more severe.

The patients record where the strongest stiffness is on the figure in which neck and shoulder is drawn and its duration they have (less than 2 weeks, 2 weeks to 3 months, more than 3 months). The patients rate the intensity of neck/shoulder stiffness by a verbal rating scale (VRS: none, weak, moderate, strong, very strong) and on a 100 mm visual analogue scale (VAS) ranging from 0 (no neck/shoulder stiffness) to 100 (the most severe neck/shoulder stiffness imaginable). The unilateral neck/shoulder in which the patients have stiffness or feel more stiffness than the other side is decided to treat before treatment.

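### The primary change-score regression does not name baseline stiffness as a covariate; if it is left out, precision is lost and chance baseline differences stay in the estimate

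*Protocol article*

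**What the plan says.** The Statistical analysis section of the protocol article sets the method ("Multiple regression analysis will be applied for data analysis") and the dependent variable and factor ("We will use pre- and post-treatment score changes as primary outcome, and treatment modes"). The four treatment modes are the three needle types and the no-treatment control. On covariates it says: "Additional covariates will include age, gender and other related potential confounders".

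Under Primary measurements there are two time points: "Improvement of neck/shoulder stiffness score immediately and 24 hours after the treatment are primary outcomes". A baseline value exists for every patient. In the section on evaluation before treatment, "The patients rate the intensity of neck/shoulder stiffness by a verbal rating scale" and also mark a 100 mm VAS.

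The article gives no pre-post correlation, standard deviation, target effect or power calculation.

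**The concern.** In a pre-post design the baseline score usually predicts change well, and there are reasons to expect that here. The inclusion criteria set no minimum intensity of stiffness and the VAS stops at 0, so a patient who enters at 15 mm cannot improve by more than 15 mm. The Background itself gives regression to the mean as a reason for the no-treatment arm. The Randomisation section describes a random-number table without stratification by severity, so any chance imbalance is left for the analysis to handle.

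The covariate sentence names two variables of less obvious relevance and does not mention baseline stiffness. A model of change without baseline has two costs. The treatment contrasts have wider intervals than the collected data allow. In any one realised randomisation, an arm that happens to start stiffer will tend to show more improvement whatever the treatment.

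**Working it through.** **Inputs from the article.** There are 400 patients in four arms ("400 patients with functional neck/shoulder stiffness are randomly assigned to four treatment groups"). With 100 sets for each of the three needle types, 400 − 300 = 100 remain for no treatment, so each pairwise contrast is 100 against 100.

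**Assumptions.** Change is the difference between the two ratings. Pre and post SD are equal and set to 1. The test is two-sided at 5%. The pre-post correlation rho runs from 0.3 to 0.9. There is no stated figure to reproduce.

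**Step 1, residual variance per patient.**
- Change score: 2(1 − rho)
- Baseline-adjusted: 1 − rho²
- Ratio adjusted/change: (1 − rho)(1 + rho) / [2(1 − rho)] = (1 + rho)/2

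**Step 2, detectable difference and power.** The difference detectable with 80% power is 2.802 × √(2 × variance/100), in SD units. The power column is the power of the adjusted analysis at the difference where the change score has 80%. The last column is the number per arm that gives the adjusted analysis the precision of 100 per arm on the change score.

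| rho | Var change | Var adjusted | Ratio | Detectable, change | Detectable, adjusted | Power, adjusted | Equivalent n per arm |
|---|---|---|---|---|---|---|---|
| 0.3 | 1.40 | 0.91 | 0.65 | 0.47 | 0.38 | 93.5% | 65 |
| 0.5 | 1.00 | 0.75 | 0.75 | 0.40 | 0.34 | 89.9% | 75 |
| 0.7 | 0.60 | 0.51 | 0.85 | 0.31 | 0.28 | 86.0% | 85 |
| 0.9 | 0.20 | 0.19 | 0.95 | 0.18 | 0.17 | 82.0% | 95 |

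**Step 3, chance imbalance.** Given a baseline difference D between two arms, the expected change-score contrast is the true effect minus (1 − rho) × D. With 100 per arm, the SE of D is √(2/100) = 0.141 SD, so its 95% range is ±1.96 × 0.141 = ±0.28 SD. At the edge of that range the shift is:
- rho 0.3: 0.7 × 0.277 = 0.19 SD
- rho 0.5: 0.5 × 0.277 = 0.14 SD
- rho 0.7: 0.3 × 0.277 = 0.08 SD
- rho 0.9: 0.1 × 0.277 = 0.03 SD

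D averages zero over randomisations, and so does the shift.

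**Step 4, check by simulation.** In 4,000 simulated two-arm trials at rho 0.5 with 100 per arm, the variance ratio was 0.754 (formula: 0.75). The slope of the estimate on D was −0.50 unadjusted and 0.00 adjusted.

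**Step 5, unequal variances.** In general, Var(change) − Var(adjusted) = SD_pre² × (1 − b)², where b = rho × SD_post/SD_pre is the slope of post on pre. The loss is zero only when b = 1, for example rho 0.8 with an SD ratio of 1.25. Otherwise there is some loss.

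**The case against.** The strongest objection is that the article nowhere says baseline is omitted. Its covariate list is open, a change score in a regression is compatible with baseline adjustment, and a condensed article may leave the full list to an analysis plan that is not shown. This stands as a limit on the wording: the point concerns a covariate left unnamed, not one shown to be absent. It does not remove the point, because the article chose to fix the outcome and name covariates and did not settle the one most closely tied to that outcome.

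Second, a change-score analysis of a randomised comparison is valid. That is correct. The loss is in precision and in conditional error, not in systematic bias.

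Third, rho could be high. The first post-treatment rating follows a session with only 10 minutes of needle retention. At rho 0.9 the variance gain is 5% and power goes from 80% to 82%. This also stands, and the table shows it.

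A reader might further infer that the open covariate clause would let pain, de-qi, satisfaction or treatment guesses into the primary model, or that covariates will be picked after unblinding. The article does not support either reading. Those ratings are not collected in the no-treatment arm, so they could not enter a four-arm model without losing that arm. Guesses are assigned to subgroup analyses in the Discussion. The article says when the bags are opened, but not that covariates are chosen afterwards.

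**Conclusion.** The point holds in a limited form. Baseline stiffness is measured in everyone, is neither named nor excluded as a covariate, and should be named. If it is left out, the variance of each pairwise contrast is 1.54, 1.33, 1.18 or 1.05 times what it need be at rho 0.3, 0.5, 0.7 or 0.9. Within the 95% range of chance baseline differences, the shift in the estimate is at most about 0.19, 0.14, 0.08 or 0.03 SD.

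These sizes rest on equal pre and post variance and on an assumed rho. The article gives neither, so the actual loss cannot be stated. That baseline is a strong predictor of change is a reasoned expectation, not a documented figure. It would be too strong to say that the plan leaves baseline out or that its primary estimate is biased. This is an inexpensive improvement that should be made; it does not invalidate the trial.

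**What to change.** State in the analysis plan: *At each time point (immediately and 24 hours after treatment), the primary model regresses the post-treatment stiffness VAS, or its change from baseline, on treatment arm (four levels), with baseline stiffness VAS, age and sex as covariates. Any further covariates are limited to variables recorded before treatment and are listed before the bags are opened.*

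Once baseline is in the model, the post score and the change score give the same treatment contrast, so the sponsor can keep change as the reported outcome. If the full plan already contains this, pointing to it is enough.

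The cost is one sentence. The baseline VAS is already collected, no extra patients are needed, and the article places the opening of the bags after all 400 treatments, so the list can be fixed blind to allocation.

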Single-blind RCTs using single-blind acupuncture placebo/sham devices have been considered the most rigorous method for investigating the efficacy of acupuncture [10-13]. However, single-blind design has the potential to produce biases from unmasked practitioners, and evidence obtained under single-blind conditions is arguably insufficiently rigorous [14-21]. Practitioner blinding has been absent in acupuncture research and it may be crucial in acupuncture research to meet the gold standard of double-blind RCTs whereby the specific effects of interventions can be distinguished under double-blinding conditions from non-specific effects [22]. In acupuncture research, however, the gold standard was considered almost impossible to achieve because blinding an acupuncturist is very difficult due to the nature of the procedure [10-15]. To solve this methodological difficulty, we designed two types of non-penetrating placebo needles: one where the tip touches the skin (skin-touch placebo needles), and another where the needle tip does not reach the skin (no-touch placebo needles). We also designed a matched genuine penetrating acupuncture needle. We have evaluated them for use in clinical settings [23-29]. In this study beside genuine penetrating acupuncture we will have two placebo acupuncture controls and an additional no-treatment control. Our two placebos will allow disentanglement to what extent skin-touching plus ritual or ritual alone contributes to the non-specific effects of placebo acupuncture and allow for a precise estimate of the mechanism whereby acupuncture may work in clinical practice.

In this study, we enrol patients who had functional neck/shoulder stiffness not due to any specific disease. To determine the efficacy of acupuncture for neck/shoulder stiffness, we use the three types of aforementioned needles to perform a randomised, double-blind (practitioner-patient), placebo-controlled study. The primary aims of the present study are to assess whether acupuncture treatment with skin piercing is superior to two different placebo treatments one with skin-touching plus ritual and one with ritual alone under double-blind conditions. The two placebo controls will allow for a more precise estimate of the components of acupuncture treatment, what might be a superior placebo. The no-treatment control will allow a determination as to whether any of the treatments are superior to natural progression, spontaneous remission or regression to the mean.

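### Read as ordinary regression, the four-arm primary model gives the penetrating-versus-placebo contrasts a wrong standard error if the untreated arm's spread differs from that of the needled arms

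*Protocol article*

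**What the plan says.** Under Statistical analysis the Protocol article names the method, "Multiple regression analysis will be applied for data analysis", and the response, "We will use pre- and post-treatment score changes as primary outcome". The treatment factor has four levels, "treatment modes (penetrating treatment, skin-touch placebo treatment, no-touch placebo treatment and no-treatment control", and age, gender and other possible confounders enter as covariates. No variance structure or standard-error method is given.

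The Background sets the main comparison: penetrating needles are to be shown "superior to two different placebo treatments one with skin-touching plus ritual and one with ritual alone under double-blind conditions". The untreated arm has a different purpose there, which is to separate treatment effects from the natural course and regression to the mean.

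The untreated patients sit in a chair and then rate again: "For the no-treatment control group, after the 10 min of no-treatment period the patients report the same items". Improvement immediately and at 24 hours are both primary outcomes.

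**The concern.** Ordinary multiple regression estimates one residual variance and uses it for every contrast. The arms here differ in kind. Three receive a needling procedure, and patients may respond to it differently; the planned analyses by treatment guess, and the planned discussion of de-qi, treat such differences as likely. The fourth arm receives nothing and rates again after 10 minutes. Equal spread across all four arms is therefore a doubtful default, above all at the immediate assessment.

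Equal allocation does not protect the placebo contrasts, because the untreated arm is not part of them and yet feeds their error term. If its spread is smaller, the intervals for penetrating versus placebo are too narrow and superiority is declared too often, while the contrasts with no treatment lose power. If its spread is larger, both effects reverse. The responder chi-square test in the same section compares only the three needled arms, so the plan already keeps the untreated arm out of the placebo question there, but not in the primary regression.

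**Working it through.** **Inputs from the article.** "400 patients are randomly assigned to penetrating, skin-touch placebo, no-touch placebo treatment or no-treatment control", and "we prepared 100 sets of four genuine acupuncture needles for penetrating treatment", with the same number of sets for each placebo. The untreated arm is therefore 400 − 300 = 100. This agrees with six acupuncturists treating 50 patients each: 6 × 50 = 300, and 300 + 100 = 400. The article states no SD, alpha or power, so there is no stated figure to reproduce.

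**Assumptions.** Two-sided 5% per contrast; the three needled arms share one SD, set to 1; the untreated SD is r; no covariates.

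**Pooled variance.** With equal arm sizes it is (1 + 1 + 1 + r²)/4 = (3 + r²)/4.

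**Penetrating versus a placebo.** The correct variance per patient is 1, so
- SE ratio (used/true) = √((3 + r²)/4)
- true error = 2·P(Z > 1.96 × SE ratio)

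At r = 0.5: (3 + 0.25)/4 = 0.8125; √0.8125 = 0.901; 1.96 × 0.901 = 1.767; error = 7.7%.

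**Needle versus no treatment.** The correct average variance is (1 + r²)/2, so SE ratio = √(2 × ((3 + r²)/4)/(1 + r²)). At r = 0.5: √(1.625/1.25) = √1.3 = 1.140.

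| r | SE ratio, penetrating vs placebo | True error | SE ratio, needle vs no treatment |
|---|---|---|---|
| 1.2 | 1.054 | 3.9% | 0.954 |
| 1.0 | 1.000 | 5.0% | 1.000 |
| 0.85 | 0.965 | 5.9% | 1.040 |
| 0.75 | 0.944 | 6.4% | 1.068 |
| 0.5 | 0.901 | 7.7% | 1.140 |
| 0 (limit) | 0.866 | about 9% | 1.225 |

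**Power of needle versus no treatment at r = 0.5.** With the correct SE, 80% power means a true difference of 1.96 + 0.84 = 2.80 SE. The overstated SE moves the rejection limit to 1.96 × 1.140 = 2.23 true SE. Power is then P(Z > 2.23 − 2.80) = P(Z > −0.57), about 71%.

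**Simulation check** (20,000 trials per value of r, 100 per arm). Four-arm pooling gives an error for penetrating versus a placebo of 7.8% at r = 0.5, 6.8% at 0.7, 6.2% at 0.8, 5.1% at 1 and 3.9% at 1.2. With the variance taken only from the two arms compared, the error stays between 5.0% and 5.1% throughout. A second simulation with HC3 gives 4.9–5.2% for r from 0.25 to 1.

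**Does dropping the untreated arm suffice?** Only if the needled arms have equal spread. Take illustrative SDs of 1.2, 1.0 and 0.8 for penetrating, skin-touch and no-touch. The three-arm pooled variance is (1.44 + 1 + 0.64)/3 = 1.027, while penetrating versus skin-touch needs (1.44 + 1)/2 = 1.22. The SE ratio is √(1.027/1.22) = 0.917, and the error is about 7.2%.

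**The case against.** The strongest objection is that neither condition is in the article. It says multiple regression and does not say how standard errors are computed; robust or arm-specific variances may be specified in an analysis plan that is not shown. This stands as a caution: pooling is the ordinary reading of the stated model, not a stated choice. It does not remove the point, which concerns the error term that the named model carries by default when applied to arms that differ in kind.

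The second objection concerns the spread. A reader might infer that the untreated arm does vary less, so that the trial's error rate is inflated. The documents do not support that. No SD is given for any arm. The article expects some real change without treatment, those patients know they are untreated, and the scale is bounded at 0. If r exceeds 1 the placebo contrasts become conservative. At 24 hours every arm has had a day of natural fluctuation, which pushes r towards 1. All of this stands, and it makes the point conditional.

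Third, the effect is modest: 5.9–6.4% for r from 0.85 to 0.75. An error near 8% needs an untreated SD about half that of the needled arms, and even r = 0 gives only about 9%.

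**Conclusion.** The point holds conditionally. With all four arms in one ordinary regression, any difference in spread between the untreated and needled arms makes the standard errors of the primary penetrating-versus-placebo contrasts wrong. Across r from 0.5 to 1.2, the true error at a nominal 5% runs from about 7.7% down to 3.9%. The contrasts with no treatment are distorted in the opposite direction, with a standard error about 14% too large at r = 0.5.

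These figures rest on equal needled SDs, a two-sided 5% test, 100 per arm and the pooled reading of the model; r itself is an assumption. A smaller untreated spread is plausible at the immediate assessment and less so at 24 hours. Inflation of the error rate is a possibility to guard against, not an established fact about this trial. The change is still worth making, because the remedy is valid whichever way the variances differ and so does not require r to be known.

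**What to change.** Add one sentence to Statistical analysis: all treatment contrasts, at both time points, use HC3 standard errors or a model with a separate residual variance for each arm. Settle this before the bags are opened, so that the error term is not chosen after seeing the data.

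Restricting the placebo contrasts to the three needled arms (300 patients) is only a partial substitute, because it still assumes equal spread among those arms.

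No new data are needed. The cost is somewhat fewer effective degrees of freedom. For a two-arm variance this means 2 × 100 − 2 = 198 instead of 4 × 100 − 4 = 396, which moves the two-sided 5% critical value from about 1.966 to 1.972 and is negligible.

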#### Inclusion criteria

1. Patients are 18 to 60 years old.

2. Patients have functional neck/shoulder stiffness without pain.

3. Patients have experienced receiving acupuncture and have experienced de-qi.

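### The supplementary responder test compares three needle arms without direction, so it cannot by itself show that penetrating beats either placebo, and it leaves out the no-treatment arm

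*Protocol article*

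**What the plan says.** The Background of the protocol article gives the primary aim as to "assess whether acupuncture treatment with skin piercing is superior to two different placebo treatments", one with touch plus ritual and one with ritual alone. It also gives the fourth arm a purpose: "The no-treatment control will allow a determination as to whether any of the treatments are superior to natural progression". That sentence goes on to name two further explanations to be ruled out, remission that would have happened anyway and regression to the mean.

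The Statistical analysis section first plans a multiple regression: "We will use pre- and post-treatment score changes as primary outcome, and treatment modes", with the modes listed as "penetrating treatment, skin-touch placebo treatment, no-touch placebo treatment and no-treatment control". It then adds a responder analysis: "we will define 30% improvement of stiffness intensity on neck/shoulder after treatment as good responders", after which "the chi-square test will be used to determine whether the numbers of improved patients are different in the penetrating, skin-touch placebo and no-touch placebo" groups. The regression lists four arms and the chi-square lists three.

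The Outcomes section does not name responder rate as a primary or secondary outcome. The inclusion criterion on the condition, "Patients have functional neck/shoulder stiffness without pain", sets no minimum score. The two sections on patients' evaluation after treatment say that no-treatment patients report the same stiffness items immediately and at 24 hours.

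**The concern.** The aim is directional and pairwise: penetrating better than skin-touch, and penetrating better than no-touch. The responder test asks only whether the three proportions are all equal. It can be significant because no-touch is poor while penetrating and skin-touch are alike, or because penetrating is the worst arm. The trial has two placebos in order to separate touch from piercing, so a pattern in which touch works and piercing adds nothing is one that it was built to detect. The omnibus p-value does not distinguish that pattern from a benefit of piercing.

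The missing fourth arm is a second gap. A responder rate is a before-after count within an arm and includes patients who would have improved anyway. The no-treatment arm was randomised to measure that share, yet it is left out of the one analysis that reports proportions improved.

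**Working it through.** **Inputs.** From the Randomisation section: 100 needle sets for each needle arm and 400 patients over four arms, so 400 / 4 = 100 per arm. The article gives no alpha, responder rates, rating variability or baseline distribution. The two-sided 5% level, the rates and the noise SDs below are assumptions. The article states no figure for this analysis, so there is none to reproduce.

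**1. Can the test locate or sign a difference?** For counts x1, x2, x3 out of n = 100 each, with pooled proportion p and mean count m = 100p,

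X² = Σ(xi − m)² / [n p (1 − p)], on 2 df, with p-value = exp(−X²/2).

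- Counts 50/50/30: p = 130/300 = 0.4333 and m = 43.33. The numerator is 6.67² + 6.67² + 13.33² = 266.7 and the denominator is 100 × 0.4333 × 0.5667 = 24.56. X² = 10.86, p-value = 0.0044.
- Counts 30/50/50: the same three numbers in another order, so X² = 10.86 and p-value = 0.0044 again.
- Counts 50/30/30 (penetrating better than both): p = 0.3667, numerator 266.7, denominator 23.22. X² = 11.48, p-value = 0.0032.

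These patterns mean no gain over skin-touch, penetrating worst, and penetrating best. All three are significant with nearly equal p-values.

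**2. How often would this happen? (illustrative, assumed rates)** 100,000 simulated trials per scenario; the pairwise criterion is z > 1.96 in favour of penetrating.

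| True rates, penetrating/skin-touch/no-touch | Chi-square significant | Penetrating beats both placebos |
|---|---|---|
| 50/50/30% | 86% | 3% |
| 30/50/50% | 86% | 0% |
| 50/30/30% | 86–87% | 73% |

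Under 50/50/30%, penetrating does not beat skin-touch in 97% of the significant trials. The 86% depends on the assumed 20-point gap: with 50/50/40% the test is significant in only about 29% of trials.

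**3. Are the pairwise contrasts feasible at this size?** For 50% against 30% with 100 per arm, power is 83% at two-sided 0.05 and 75% at 0.025. Eighty per cent power at 0.05 needs 93 per arm.

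**4. Baseline.** If response is a 30% fall from the pre-treatment VAS, the threshold is 0.30 × baseline: 3 mm at 10 mm, 6 mm at 20 mm, 15 mm at 50 mm and 24 mm at 80 mm. With no true change and normal rating noise of SD s, the chance of being counted a responder is Φ(−0.30 × baseline / s):

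| Assumed s | Baseline 10 mm | Baseline 50 mm |
|---|---|---|
| 4 mm | 23% | about 0% |
| 8 mm | 35% | 3% |
| 15 mm | 42% | 16% |

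At s = 2 mm the 10 mm figure falls to 7%. The model ignores the scale's floor at zero, so these figures are only indicative.

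**The case against.** The strongest reply is that the chi-square is an addition to a regression containing all four arms. That model can estimate penetrating against each placebo and each treatment against no-treatment. A reader might infer that the efficacy question, or the no-treatment arm, goes unanalysed; the article does not support that. This part of the reply stands and limits the point to the responder analysis.

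A second reply is that the article does not exclude pairwise follow-up tests, which may sit in a fuller document. That is fair. But the text names one test and three arms directly after listing four, so the choice can be judged as written. The observed proportions would also help a careful reader, although the test itself would not.

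A reader might also infer that the test ignores baseline and is therefore invalid, or that 30% is a trivial change in mild cases. Neither is supported. A percentage improvement is ordinarily relative to the pre-treatment rating, and randomisation keeps an unadjusted comparison valid. Noise responders arise in every arm, so they dilute differences without favouring penetrating. The article gives no minimal important change and no baseline distribution.

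Finally, low pairwise power should not be counted against the chi-square. Under 50/40/30% it is significant in 75% of trials and both contrasts hold in 30%, but the 50% versus 40% contrast alone has only about 31% power. The proposed contrasts would face the same limit.

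**Conclusion.** The point holds for the supplementary responder analysis only. As written, that test cannot locate or sign a difference: 50/50/30 and 30/50/50 give the identical X² = 10.86, p = 0.0044. This needs no assumption beyond 100 per arm and the natural reading of the sentence as a single three-group test. The omission of the no-treatment arm is plain from the text and departs from that arm's stated purpose.

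The simulated percentages are illustrations under assumed rates and noise, not predictions. Baseline adjustment is a matter of precision, not validity. How many patients start low enough for a few millimetres to count as response is unknown. The main aim remains answerable through the regression, so this is a worthwhile improvement and not a threat to the trial.

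**What to change.** Replace the chi-square with a logistic regression:

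- **Response:** a fall of at least 30% in the stiffness-intensity VAS from baseline, defined separately for immediately after treatment and for 24 hours. This settles the scale (a change VAS is also collected) and the time point.
- **Model:** arm with four levels, plus baseline VAS.
- **Planned contrasts:** penetrating versus skin-touch and penetrating versus no-touch. Either require both to be significant for a claim of superiority over both placebos, or apply a multiplicity adjustment if one alone may support a claim (for example 0.025 each). State whether claims are made per time point, and extend the adjustment if either time point may carry the claim.
- **Supportive:** each needle arm versus no-treatment.
- **Reporting:** responder rate differences with confidence intervals for every contrast.

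The cost is analysis wording only, since stiffness is rated before treatment and at both later times in all four arms. The article describes the study as ongoing and keeps the needle types unrevealed until all 400 treatments are complete, so at publication the change could still be made before unblinding.
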